### 2.9. Outcomes

All outcome variables will be assessed at baseline (pre-test) and immediately after the 8-week intervention period (post-test). The study will evaluate physical fitness, body composition, and psychological outcomes in children aged 10–12 years using validated field-based tests and questionnaires (Figure S2). All baseline and post-intervention assessments will be completed during a single evaluation session lasting approximately 60–90 min. To minimize fatigue, physical fitness tests will be administered in a standardized order with adequate recovery periods between assessments according to established testing protocols. Participants will receive standardized instructions and verbal encouragement throughout the testing session. Familiarization trials will be provided when required by the testing protocol to ensure adequate understanding of the procedures and to promote valid test performance. Before the strength assessments, all participants will perform a standardized warm-up protocol consisting of: (i) a general warm-up including light running, skipping, heel-to-glute movements, arm circles, wrist and ankle rotations, lunges, and changes in direction; (ii) a specific warm-up for jump including controlled squats, low-intensity jumps, and lunges with trunk rotation; (iii) a specific warm-up for handgrip dynamometry involving squeezing a rubber ball and wrist flexion-extension exercises; and (iv) a specific warm-up for the medicine ball throw including shoulder rotations, light medicine ball throws, and core activation exercises.

#### 2.9.1. Primary Outcome

##### VO_2_max (Course-Navette Test)

Cardiorespiratory fitness will be assessed using the 20-m Course-Navette test, a validated field-based test widely used to estimate maximal oxygen uptake (VO_2_max) in children and adolescents [35]. Participants will run continuously between two lines separated by 20 m at progressively increasing speeds, starting at 8.5 km·h^−1^ and increasing by 0.5 km·h^−1^ every minute. The test will be terminated when participants fail to reach the line in time on two consecutive occasions or voluntarily stop due to fatigue. VO_2_max will subsequently be estimated from the final stage attained using the equation developed by Léger et al. [35].

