### 2.10. Sample Size and Power

Sample size estimation was performed using G*Power software version 3.1 [51] to ensure adequate statistical power to detect significant differences between the experimental and control groups in one of the primary outcomes of the study, maximal oxygen uptake (VO_2_max) estimated from the Course-Navette test. The calculation was based on two-tailed independent samples t-test using data reported by Alves et al. [52], who conducted a concurrent training intervention in children of similar age and intervention duration. In that study, the intervention group showed a mean increase of 1.7 mL·kg^−1^·min^−1^ in VO_2_max, whereas the control group showed a mean increase of 0.2 mL·kg^−1^·min^−1^. The pooled standard deviation of the change scores was calculated from the reported standard deviations of the intervention and control groups, 1.9 and 1.6, respectively, resulting in a pooled SD of approximately 1.76. Based on these values, the estimated standardized effect size was Cohen’s d = 0.86. Assuming an alpha level of 0.05, a statistical power of 0.80, and an allocation ratio of 1:1, the required sample size was estimated at 46 participants, with 23 participants per group. Considering a potential dropout rate of approximately 10–15%, the target recruitment will be increased to approximately 52–54 participants to maintain adequate statistical power throughout the study period.

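### Scoring the shuttle run from the final stage leaves the shuttles within a stage unused and probably costs precision in the primary outcome; how much depends on an equation slope the protocol does not give

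*Protocol article*

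**What the plan says.** Section 2.9.1 of the protocol article names one primary outcome, VO2max from the Course-Navette test. On the course it says "Participants will run continuously between two lines separated by 20 m". The speed starts at 8.5 km/h, "increasing by 0.5 km·h^−1^ every minute". The score "will subsequently be estimated from the final stage attained using the equation" of a cited source. The coefficients are not printed, and the section does not say how a part-completed stage counts.

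Section 2.10 sizes the trial on this outcome, from an earlier concurrent training study in children. In that study "the intervention group showed a mean increase of 1.7" mL/kg/min, "whereas the control group showed a mean increase of 0.2". The SDs of change were 1.9 and 1.6, "resulting in a pooled SD of approximately 1.76". From these, "the estimated standardized effect size was Cohen’s d = 0.86". With a "two-tailed independent samples t-test", alpha 0.05 and power 0.80, the result is 23 per group. The section does not say how the earlier study scored its shuttle test.

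**The concern.** The test yields finer information than the scoring rule uses. If only the stage reached enters the equation, a child who stops early in a stage and one who stops just before its end get the same stage input. The score then moves in steps of one stage.

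The trial looks for a mean difference in change of 1.7 − 0.2 = 1.5 mL/kg/min, and its planned power is only just above 0.80. A change score carries the rounding of two visits. At stake is avoidable variance in the one outcome on which the trial is sized, when the missing information could be had by writing down one more number.

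**Working it through.** **1. The plan's own figure.** Pooled variance = (1.9² + 1.6²)/2 = 3.085, so SD = 1.756. d = 1.5/1.756 = 0.854 (the plan prints 0.86). By the noncentral t, two-sided alpha 0.05 and power 0.80, d = 0.86 needs 22.2 per arm and d = 0.854 needs 22.5. Both round up to 23, which agrees with the plan. Power at 23 per arm is 0.81 in either case.

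**2. Shuttles per stage.** Shuttles in a one-minute stage = speed × 1000/60/20. At 8.5 km/h this is 7.1. At 12 km/h, taken as an illustrative later stage, it is 10.0.

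**3. Step size (assumed).** One stage is 0.5 km/h, so h = 0.5 × slope, if the equation is linear in speed. The slope is not in the document. Slopes of 2, 3, 4, 5 and 6 mL/kg/min per km/h give h = 1.0, 1.5, 2.0, 2.5 and 3.0.

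**4. Variance from rounding.** A uniform rounding error has variance h²/12. Two independent errors, one per visit, add 2 × h²/12 = h²/6 to the variance of change.

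**5. Power at 23 per arm, difference 1.5.** The document does not say whether 3.085 already contains stage rounding, so both cases are shown.
- Case A, rounding not included: whole-stage scoring gives SD = √(3.085 + h²/6).
- Case B, rounding included: removing it gives SD = √(3.085 − h²/6).

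| Step h | h²/6 | Share of 3.085 | A: SD | A: power | A: n per arm for 0.80 | B: SD | B: power |
|---|---|---|---|---|---|---|---|
| 1.0 | 0.167 | 5% | 1.80 | 0.79 | 24 | 1.71 | 0.83 |
| 1.5 | 0.375 | 12% | 1.86 | 0.76 | 26 | 1.65 | 0.86 |
| 2.0 | 0.667 | 22% | 1.94 | 0.73 | 28 | 1.56 | 0.89 |
| 2.5 | 1.042 | 34% | 2.03 | 0.69 | 30 | 1.43 | 0.94 |
| 3.0 | 1.500 | 49% | 2.14 | 0.64 | 33 | 1.26 | 0.98 |

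Shuttle-level scoring still rounds, to about h/8. Allowing for that changes the case B powers by less than 0.002.

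**6. Check by simulation.** In 20,000 simulated trials per setting, with 23 per arm, an assumed baseline SD of 5 and a latent SD of change of 1.76, values were rounded down to whole steps at both visits. The mean group difference stayed at about 1.50 at every step size. The SD of change rose to 1.81 at h = 1.0 and 2.14 at h = 3.0, as h²/6 predicts. Power was 0.79 and 0.64.

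**The case against.** **The rule may be less strict than it looks.** The text refers to the final stage attained. It does not say that part-stages are ignored, and a journal article may leave such detail to a fuller protocol or test manual. This stands in part: no credit for a part-stage is the plain reading, not an explicit statement. But a scoring rule for the primary outcome is stated, and it is stated by stage.

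**The step may be small.** This stands. A reader might infer that one stage is worth at least the 1.5 mL/kg/min sought. That needs a slope of 3 or more per km/h, and the document gives no slope. At h = 1.0 the cost or gain is about 2 points of power.

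**A step larger than the effect does not hide the effect.** This also stands. A gain of several shuttles can score zero, but a gain of one shuttle across a stage boundary scores a full step, and on average these balance. The cost is variance, not bias.

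**The power calculation may already include the rounding.** If the earlier study scored by stage, 1.76 contains it and planned power remains 0.81. A reader might infer that 23 per arm is too few. The document does not support that, because it does not say how that study scored the test.

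**A published equation applied as published is defensible.** True. An interpolated speed makes absolute values slightly less comparable with other studies. That is a reason to keep the whole-stage value in the report, but it does not justify discarding the shuttle count.

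**Conclusion.** The point holds as a loss of precision. On its plain reading, section 2.9.1 leaves the 7 to 10 shuttles within a stage unused, which adds about h²/6 to the variance of each child's change and does not bias the comparison.

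For assumed slopes of 2 to 6 mL/kg/min per km/h, finer scoring helps in both cases. It lifts power from 0.81 to about 0.83–0.98 if the planning SD includes stage rounding, or avoids a fall to about 0.79–0.64 if it does not. The document cannot settle which case applies or where in the range the slope lies. The figures also rest on an equation linear in speed and on independent, uniform rounding errors at the two visits.

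No error in the stated sample size is claimed. The change is worth making because it is cheap and the planned power has little slack.

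**What to change.** - Record the last completed shuttle as well as the stage, at both visits.
- Define the final speed as: speed of the last full stage + 0.5 × (shuttles completed in the next stage / shuttles in that stage). Apply the equation to this speed, in the same way at both visits. State the rule for a child who stops within the first stage.
- Report the whole-stage VO2max and the total number of shuttles as supportive results, and say whether the whole-stage value uses the last stage entered or the last stage completed.
- In section 2.10, state how the earlier study scored its test, if this can be found, so that the meaning of the 1.76 is clear.

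The cost is one more number on the score sheet, with no added testing for the children. The downside is that the published equation receives an interpolated speed, so absolute values become slightly less comparable with other studies. The supportive whole-stage result covers that.

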#### 2.9.2. Secondary Outcomes

##### Lower-Limb Explosive Strength (Countermovement Jump Test)

Lower-limb explosive strength will be assessed using the countermovement jump (CMJ) test described by Bosco et al. [36]. Participants will begin from an upright standing position with their hands placed on the waist and will perform a maximal vertical jump following a rapid downward movement until approximately 90° knee flexion. Three attempts will be performed, and the highest jump height will be recorded. Jump performance will be measured using the ADR Jumping system (ADR, Toledo, Spain).

##### Maximal Isometric Handgrip Strength (Handgrip Dynamometry)

Maximal isometric handgrip strength will be assessed using a digital dynamometer (Takei 5401, Takei Scientific Instruments Co., Ltd., Niigata, Japan) adjusted to the participant’s hand size. Participants will perform the test with the arm extended parallel to the trunk while exerting maximal force. Following one familiarization attempt and one minute of recovery, two attempts will be performed alternately with both hands. The best value obtained for each hand will be recorded [37].

##### Horizontal Lower-Body Explosive Strength (Standing Long Jump)

Horizontal explosive strength will be assessed using the standing long jump test. Participants will perform a maximal horizontal jump using both feet simultaneously without a preparatory step. The longest distance achieved will be measured using a measuring tape from the starting line to the nearest heel at landing. Two attempts will be performed, and the best result will be recorded [38].

##### Upper-Body Explosive Strength (Medicine Ball Throw)

Upper-body explosive strength will be assessed using a 2-kg medicine ball throw test. Participants will stand upright holding the medicine ball with both hands above the head and will throw it forward as far as possible without crossing the designated line. Two attempts will be performed, and the best distance achieved will be recorded [39].

##### Core Muscular Endurance (Plank Test)

Core muscular endurance will be assessed using the plank test. Participants will maintain a prone plank position supported by forearms and toes while maintaining a neutral spine and body alignment. The test will end when participants fail to maintain the correct position after verbal correction. The maximum time maintained in the correct position will be recorded [40].

##### Muscular Endurance and Functional Capacity (Burpees Test)

Muscular endurance and functional capacity will be evaluated using a burpee test performed for one minute. Participants will complete as many correctly executed burpees as possible during the established time period. The total number of repetitions completed will be recorded [41].

##### Cardiovascular Recovery Capacity (3-min Step Test)

Cardiovascular recovery capacity will be assessed using a 3-min step test performed on a 30-cm step. Participants will step continuously at a standardized cadence throughout the test duration. Heart rate will be recorded immediately after exercise and following 1 min of passive recovery in order to evaluate post-exercise cardiovascular recovery [42].

##### Age and Sex

Participants’ age and sex will be recorded before baseline assessments.

##### Body Weight, Height, and Body Mass Index (BMI)

Body weight and height will be assessed according to the ALPHA-Fitness battery procedures [43]. Body weight will be measured using an electronic scale (Tanita RD-545; Tanita Corporation, Tokyo, Japan), and height will be measured using a portable stadiometer (SECA 213; Seca GmbH & Co. KG, Hamburg, Germany). Body mass index (BMI) will subsequently be calculated as body weight in kilograms divided by height in meters squared (kg/m^2^).

##### Body Fat Percentage

Body fat percentage will be assessed using bioelectrical impedance analysis according to the International Society for the Advancement of Kinanthropometry (ISAK) guidelines. Participants will be assessed barefoot and wearing light clothing following standardized anthropometric procedures [44].

Psychological assessments will be administered on the same day as the physical evaluations at baseline and post-intervention. Participants will complete the questionnaires in a quiet and controlled environment under researcher supervision.

##### Anxiety (State–Trait Anxiety Inventory for Children; STAIC)

Anxiety will be assessed using the State–Trait Anxiety Inventory for Children (STAIC), developed by Spielberger et al. [45] and adapted into Spanish by Gualberto et al. [46]. The questionnaire evaluates both state anxiety and trait anxiety through 40 items divided into two subscales. Previous studies have shown adequate internal consistency for the instrument, with a Cronbach’s alpha coefficient of approximately 0.70.

##### Daily Stress (Children’s Daily Stress Inventory; IECI)

Stress levels will be assessed using the Inventario de Estrés Cotidiano Infantil (IECI; Children’s Daily Stress Inventory) developed by Trianes et al. [47]. The IECI is composed of 22 dichotomous items (yes/no response format) designed to evaluate daily stress in the domains of health, school, and family. The instrument showed adequate internal consistency, with a Cronbach’s alpha coefficient of 0.81 for the total scale, while subscale coefficients ranged from 0.62 to 0.68.

##### Self-Esteem (Rosenberg Self-Esteem Scale)

Self-esteem will be assessed using the Rosenberg Self-Esteem Scale [48], adapted into Spanish by Vázquez and Rodríguez [49]. The scale includes 10 items answered using a 4-point Likert scale and showed adequate internal consistency (Cronbach ’s α = 0.87).

Although all psychological instruments selected for this study have been previously validated for use in pediatric populations, some measures may show lower sensitivity in younger children. Therefore, the results of the psychological assessments will be interpreted taking participants’ age and developmental characteristics into consideration [50].

##### Perceived Exertion (Pictorial Children’s Effort Rating Table; PCERT)

Perceived exertion during exercise will be assessed using the Pictorial Children’s Effort Rating Table (PCERT) [34]. Participants will identify the image corresponding to their perceived level of effort after exercise sessions. The instrument showed adequate reliability for assessing perceived exertion in children (Cronbach’s α => 0.70).

### 2.10. Sample Size and Power

Sample size estimation was performed using G*Power software version 3.1 [51] to ensure adequate statistical power to detect significant differences between the experimental and control groups in one of the primary outcomes of the study, maximal oxygen uptake (VO_2_max) estimated from the Course-Navette test. The calculation was based on two-tailed independent samples t-test using data reported by Alves et al. [52], who conducted a concurrent training intervention in children of similar age and intervention duration. In that study, the intervention group showed a mean increase of 1.7 mL·kg^−1^·min^−1^ in VO_2_max, whereas the control group showed a mean increase of 0.2 mL·kg^−1^·min^−1^. The pooled standard deviation of the change scores was calculated from the reported standard deviations of the intervention and control groups, 1.9 and 1.6, respectively, resulting in a pooled SD of approximately 1.76. Based on these values, the estimated standardized effect size was Cohen’s d = 0.86. Assuming an alpha level of 0.05, a statistical power of 0.80, and an allocation ratio of 1:1, the required sample size was estimated at 46 participants, with 23 participants per group. Considering a potential dropout rate of approximately 10–15%, the target recruitment will be increased to approximately 52–54 participants to maintain adequate statistical power throughout the study period.

### 2.11. Statistical Analysis

Statistical analyses will be performed using IBM SPSS Statistics version 26.0 (IBM Corp., Armonk, NY, USA) or equivalent statistical software. Descriptive statistics will be calculated for all study variables and presented as mean ± standard deviation or median and interquartile range for continuous variables, and as frequencies and percentages for categorical variables. Data distribution will be checked using graphical methods and, when appropriate, the Shapiro–Wilk test. To account for the repeated-measures design, intervention effects will be analyzed using linear mixed-effects models. Separate models will be performed for each outcome, including group, time, and the group × time interaction as fixed effects, and participant ID as a random effect. Models will be adjusted for age, sex, and growth-related variables such as baseline height, body mass, and body mass index. Effect sizes will be calculated using partial eta squared (η^2^p) and interpreted as small (0.01), medium (0.06), or large (0.14) effects. In addition, Hedges’ g effect sizes will be calculated to estimate the magnitude of within-group changes and between-group differences in pre–post changes [53]. All effect-size estimates will be reported with 95% confidence intervals whenever appropriate.

Analyses will primarily follow the intention-to-treat principle. Linear mixed-effects models will be used because they allow the inclusion of all randomized participants with available observations and can accommodate incomplete outcome data under the missing-at-random assumption. Therefore, no imputation procedures are planned unless the amount or pattern of missing data suggests otherwise. A per-protocol analysis will also be conducted as a sensitivity analysis including participants who attend at least 80% of the intervention sessions.

Relevant changes in lifestyle-related factors during the intervention period, including the initiation of new structured physical activity outside the study, substantial changes in diet, sleep routines, or screen time, will be recorded when reported by families and considered when interpreting the results. Sensitivity analyses will be performed when appropriate and feasible.

Considering the number of physical fitness, body composition, and psychological outcomes included in the study, the possibility of inflated type I error due to multiple comparisons cannot be excluded and will be considered when interpreting the results. This issue will also be acknowledged as a study limitation. Statistical significance will be established at *p* < 0.05 for all analyses.

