Several limitations should also be acknowledged. First, the recruitment from a single educational center may limit the generalizability of the findings. Furthermore, the intervention will be conducted in a specialized HIFCT facility rather than within the school environment. Although this setting allows standardized implementation, professional supervision, and access to appropriate equipment, it may limit the ecological validity, scalability, and direct transferability of the findings to typical school-based physical activity programmes. Second, although the intervention duration was selected based on previous studies [15,16], it may be insufficient to detect stable adaptations in some body composition and psychological outcomes. Third, the use of a passive control group, while facilitating implementation under real-world school conditions, may limit the ability to distinguish the specific effects of the HIFCT intervention from the potential influence of increased supervision, social interaction, motivation, or participation in structured physical activity. Moreover, due to the nature of the intervention, participant and trainer blinding is not feasible, which may increase the risk of performance bias. In addition, although age- and growth-related variables will be considered in the analyses, the influence of normal growth and maturation during childhood cannot be completely excluded. Finally, the inclusion of multiple physical fitness, body composition, and psychological outcomes may increase the risk of type I error due to multiple statistical comparisons. Although this comprehensive assessment represents one of the strengths of the study, findings, particularly those related to secondary outcomes, will be interpreted with appropriate caution. Overall, the present study may provide valuable information regarding the feasibility, safety, and potential effects of HIFCT in school-aged children. The findings may contribute to the design of future randomized controlled trials and help inform evidence-based exercise recommendations for pediatric populations.

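### As ordinarily read, the mixed model's growth adjustment leaves the treatment effect essentially unchanged, and letting the arms differ freely at baseline gives up some precision

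*Protocol article*

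**What the plan says.** Section 2.11 fits a separate linear mixed model for each outcome, "including group, time, and the group × time interaction as fixed effects, and participant ID as a random effect". It then says: "Models will be adjusted for age, sex, and growth-related variables such as baseline height, body mass, and body mass index". Group × time is the only interaction named. Neither the outcome's own baseline as a covariate nor an equal-baseline constraint is mentioned. Mixed models are chosen partly because they "can accommodate incomplete outcome data under the missing-at-random assumption".

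Section 2.9 gives two assessments, before and immediately after the 8 weeks. Section 2.4 places randomisation after the baseline evaluations and stratifies it by sex and age. In section 2.9.2, BMI is calculated from the measured weight and height.

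On sample size (section 2.10): "The calculation was based on two-tailed independent samples t-test", using the mean changes and SDs of change from an earlier trial. The Discussion qualifies the influence of growth and maturation with "although age- and growth-related variables will be considered in the analyses", while conceding that this influence cannot be fully ruled out.

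**The concern.** A reader of sections 2.11 and 3 would take the treatment effect to be adjusted for age, sex and body size. On the ordinary reading of the model, those terms explain differences in level between children. They do not act on the contrast that measures the intervention.

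The model also gives each arm its own free baseline mean. Baseline is measured before randomisation, so any difference there is chance. Leaving it free means a chance imbalance passes into the change score through regression to the mean, and precision is lost. That matters in a trial of 46 evaluable children with many outcomes, some of which may have a modest pre-post correlation.

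Two smaller points of wording go with this. Height, mass and BMI are listed together although the third is a function of the first two. In the body mass and BMI models, the baseline value would be both a covariate and the time-0 response.

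**Working it through.** **Inputs.** From section 2.10: mean changes 1.7 and 0.2 mL/kg/min (difference 1.5), SDs of change 1.9 and 1.6, two-sided alpha 0.05, power 0.80, 1:1 allocation, 23 per arm, 10–15% dropout, target 52–54. The pre-post correlation ρ is not in the document and is assumed, from 0.5 to 0.95.

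**1. The plan's own figure.** Pooled SD = √((1.9² + 1.6²)/2) = 1.756. Then d = 1.5/1.756 = 0.854 (0.86 stated). At 23 per arm the noncentrality is 0.854 × √(23/2) = 2.90 on 44 degrees of freedom. Power is 0.808 (0.814 at d = 0.86), and 23 is the smallest number per arm that reaches 0.80. The stated 46 reproduces.

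**2. What group × time estimates.** Write the response of child i at time t (0 or 1) as

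Y = α + βG + γt + δ(G × t) + λX + b + e,

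with X the baseline covariates and b the child's random intercept. The child's change is γ + δG + (e₁ − e₀). Both X and b cancel. The child's sum of the two visits also contains δ, but the free group main effect β absorbs whatever the sum says about the arms. With complete pairs, δ is therefore estimated from the changes alone: it is the difference in mean change, whatever X contains.

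**3. Numerical check.** There were 80 simulated trials per setting, with SD of change 1.756 and covariates assumed to explain 30% of the between-child variance.

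- Complete data, 23 per arm: adding age, sex, height, mass and BMI as main effects moved the estimate by less than 10⁻¹³. The mean SE stayed at 0.514 (ρ = 0.6) and 0.517 (ρ = 0.8).
- 27 per arm with 15% random dropout: the estimate moved by 0.03–0.04 on average (largest 0.24 in a single trial) against an SE of about 0.51. The mean SE went from 0.5083 to 0.5080 (ρ = 0.6) and from 0.5193 to 0.5181 (ρ = 0.8).

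**4. Precision given up.** With equal variances σ² at both visits, the change score has variance 2σ²(1 − ρ), and the baseline-adjusted post-test value has σ²(1 − ρ²). The ratio is (1 + ρ)/2. Holding the SD of change at 1.756, the effective d becomes 0.854/√((1 + ρ)/2). The few degrees of freedom spent on covariates are ignored here.

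| Assumed ρ | Excess SE of planned analysis | Power at 23 per arm, baseline-adjusted | Per arm for 0.80 |
|---|---|---|---|
| 0.5 | 15.5% | 0.90 | 18 |
| 0.6 | 11.8% | 0.89 | 19 |
| 0.7 | 8.5% | 0.87 | 20 |
| 0.8 | 5.4% | 0.85 | 21 |
| 0.9 | 2.6% | 0.83 | 22 |
| 0.95 | 1.3% | 0.82 | 22 |

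The planned analysis has 0.81 throughout and needs 23 per arm.

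**5. Which remedies deliver.** Mean SE in the complete-data simulations:

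| Analysis | ρ = 0.6 | ρ = 0.8 |
|---|---|---|
| As planned | 0.514 | 0.517 |
| Common baseline mean, five covariates | 0.455 | 0.486 |
| ANCOVA on baseline plus five covariates | 0.480 | 0.515 |
| As planned plus covariate × time terms | 0.544 | 0.542 |

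The constraint gains in both settings. ANCOVA carrying all five covariates gains almost nothing at ρ = 0.8, which argues for a short list. Covariate × time terms make the adjustment act on change but cost precision here, where change was simulated as independent of the covariates.

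**The case against.** **The form of the covariates is not stated.** Section 2.11 says only that models are adjusted; main effects alone is an inference. That is true, and an analysis plan could add covariate × time terms. But the text lists its fixed effects and names one interaction, so main effects is how most analysts would program it. The body-size list is also introduced as examples, so using all three together is not a firm commitment.

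**The adjustment is not wholly inert.** With dropout, main-effect covariates do enter the estimate. This stands, but the shift is small against the SE and the SE hardly moves.

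**Nothing planned is lost.** The trial was sized on change scores and the model estimates a difference in change scores. Design and analysis agree, the 0.80 target is met, and allocation is stratified by sex and age. All of this stands. A reader might infer that the trial is biased or underpowered; the documents support neither. Nor does the model ignore the baseline value: a change score subtracts it, though with a fixed weight of one.

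**Redundant size covariates do no harm to the treatment effect.** Correct. If the covariates leave group × time alone, collinearity among them cannot damage it. It is a reason for a tidier list, not evidence of a wrong result.

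**Growth is already disclosed as a limitation.** In part. The Discussion concedes some residual influence after adjustment; it does not say that the adjustment leaves the effect unchanged.

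**Conclusion.** The point holds in a limited form. As ordinarily read, the model estimates the difference in mean change. The stated adjustment for age, sex and body size leaves that estimate and its SE unchanged with complete pairs, and almost unchanged at the planned dropout. Calling the treatment effect growth-adjusted is therefore inaccurate.

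Validity and planned power are intact. What is given up is precision: about 1% to 15% of the SE, or one to five children per arm, for ρ from 0.95 down to 0.5. That size rests on an assumed correlation, equal variances at the two visits, and the protocol's SD of change. At high correlations the gain is slight. This is an improvement worth making before data are seen, not the repair of an invalid analysis.

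**What to change.** 1. Keep the mixed model but constrain the arms to a common baseline mean: time and group × time, no group main effect, with sex and age (the stratification factors) as covariates. This keeps every randomised child with data. With the group main effect gone, the treatment contrast also draws on between-child information, so these covariates do contribute. Alternatively, use ANCOVA of the post-test value on its baseline value, sex and age.
2. Do not list height, body mass and BMI together.
3. Word the body mass and BMI models separately: in a mixed model, do not enter the outcome's own baseline as a covariate while it is also the time-0 response.
4. Either let a small number of prespecified growth covariates act on change, without promising better precision, or stop describing the treatment effect as growth-adjusted in sections 2.11 and 3.

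The cost is analysis wording and a few residual degrees of freedom. No new data and no change in sample size are needed.
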